## Abstract

**Background:**

Successful pain management after outpatient surgery requires proper education leading to correct decisions on the analgesics use at home. Despite different strategies adopted, up to ½ of patients receive little or no information about the treatment of postoperative pain, 1/3 of them are not able to follow postoperative analgesia instructions. This leads to higher rates of unmet needs in pain treatment, post-discharge emergency calls, and readmissions. Structured educational interventions using psychological empowering techniques may improve postoperative pain management. We hypothesize that preoperative education on use of an improved pain scale to make correct pain management decisions will improve the quality of post-operative pain management at home and reduce analgesics-related side effects.

**Methods:**

A total of 414 patients scheduled for an outpatient orthopedic surgery (knee/shoulder arthroscopic interventions) are included in this randomized (1:1) controlled trial. Patients in the control arm receive standard information on post-discharge pain management. Patients in the experimental arm receive structured educational intervention based on the rational perception of postoperative pain and discomfort (anchoring and improved pain scale), and the proper use of analgesics. There is no difference in post-discharge analgesics regimen in both arms. Patients are followed for 30 days post-discharge, with the primary outcome expressed as total pain relief score at 5 days. Secondary outcomes include the incidence of severe pain during 30 days, changes in sleep quality (Pittsburg Sleep Quality Assessment), and patients’ perception of postoperative pain management assessed with the International Pain Outcomes questionnaire at day 30 post-discharge.

**Discussion:**

The developed intervention, based on an improved pain scale, offers the advantages of being non-surgery-specific, is easily administered in a short amount of time, and can be delivered individually or in-group, by physicians or nurses.

**Trial registration:**

ClinicalTrials.govNCT03754699. Registered on November 27, 2018.

**Supplementary Information:**

The online version contains supplementary material available at 10.1186/s13063-022-06387-6.

## Administrative information

Note: the numbers in curly brackets in this protocol refer to SPIRIT checklist item numbers. The order of the items has been modified to group similar items (see http://www.equator-network.org/reporting-guidelines/spirit-2013-statement-defining-standard-protocol-items-for-clinical-trials/).

## Introduction

### Background and rationale {6a}

The rate of ambulatory surgery varies between 30% and more than half of all surgery in high-income countries involving all age patients [1, 2]. Postoperative pain management and nausea-vomiting are the main barriers for the successful outpatient track and are the main issues for the first 72 h after discharge [3, 4].

Multiple approaches for the outpatient pain management include preemptive and multimodal anesthesia, pharmacological treatment, coordination and follow-up solutions, ambulatory pain specialist involvement, and patient education [5–7]. Caregivers should provide proper information covering the modalities of post-discharge analgesia [8].

Structured education intervention using psychological techniques to enhance engagement and behavior was found to be effective in different chronic conditions [9, 10]. For instance, pain knowledge and attitude improvements have a positive effect on pain intensity in cancer patients who are already on opioid therapy at home [11]. In hospitalized orthopedic patients such intervention improves patient-reported outcomes (PRO) [12]. However, no robust evidence is available on its real benefit in the outpatient settings [13].

Self-management of postoperative pain at home is based on auto-evaluation of pain intensity. Pain intensity scales for auto-evaluation (11 items numeric, analogs or visual, simplified visual pain scales) are proposed to patients in order to help manage pain control at home. However, at least 40% of patients are unable to use it correctly in extra hospital settings [14], and this inability is more marked in a vulnerable population [15, 16].

Preoperative instruction on the use of a pain scale was found to improve the patient's ability to self-report pain [17]. Nevertheless, patients in an outpatient clinic would prefer other than a simple numeric scale to assess their pain [18]. Patients choose to use comprehensive pain scales, which rationalize their perception of pain and discomfort, probably preventing from emotional amplification and catastrophizing [19].

### Objectives {7}

We hypothesize that an educational intervention based on the rational perception of postoperative pain and discomfort, and the proper use of analgesics would improve the quality of pain management at home and reduce analgesics-related side effects.

The study evaluates the effectiveness of an educational intervention on pain relief at home in outpatient orthopedic surgery, compared to standard care. The pain relief is assessed during the first five post-discharge days (primary outcome), then on the 10th, 20th and 30th days after surgery (secondary outcome). The prevalence of severe pain (as reported by participants), medication use, side effect of medication, changes in sleep quality, the incidence of neuropathic pain at day 30 after surgery, and overall satisfaction at day 30 will be assessed as a part of secondary objectives.

### Trial design {8}

PELOPS is a single-center prospective randomized controlled two-group superiority trial with parallel assignment. This manuscript describes the study protocol and the beginning of the trial in the setting of outpatient orthopedic surgery

## Methods: Participants, interventions, and outcomes

### Study setting {9}

This study is performed at the Hopital de la Croix Rousse, Hospices Civils de Lyon, tertiary university hospital in France. Three departments are involved in the trial - Department of Orthopedic Surgery, Department of Anesthesia, and Outpatient Surgery Department.

### Eligibility criteria {10}

Adult patients (age more than 18 years old), scheduled for elective outpatient orthopedic surgery in will be recruited. Surgical interventions include knee and shoulder arthroscopy, cruciate ligament repair, and medial patellofemoral ligament (MPFL) repair. These interventions are frequent and are known to produce moderate to severe pain in the early postoperative period [20].

Non-eligible are pregnant or breast-feeding women, patients with contraindication for acetaminophen and anti-inflammatory drugs, with chronic pain beyond the surgical site, outpatient knee and hip arthroplasty (specific education and at-home program already in place), patients without social security coverage, non-French speaking, unable to consent, disagree to participate.

### Who will take informed consent? {26a}

Patients will be recruited during the pre-anesthesia visit by a physician anesthesiologist. After meeting inclusion criteria, each patient will be orally informed about the study protocol first. Agreed patients will sign a written consent form and will be randomized to receive either standard information on postoperative pain management or structured education intervention. A physician anesthesiologist, performing pre-anesthesia evaluation and patients’ inclusion, collects the written consent.

### Additional consent provisions for collection and use of participant data and biological specimens {26b}

In a case of an ancillary study with the data collection not covered in the original informed consent form, the new signed consent has to be obtained from every participant. In a case of retrospective use of already generated data, stored in the institutional Electronic Health Record, all patients should be informed about their data use according to the European General Data Protection Regulation. No biological specimens will be collected in this trial.

## Interventions

### Explanation for the choice of comparators {6b}

#### Standard pain information

The standard recommendation on postoperative pain management for outpatient procedures is based on the recommendation of the French National Agency for Medication and Medical Products Safety (Agence nationale de sécurité du médicament et des produits de santé –ANSM) and the French Society of Anesthesia (SFAR), available through the site of the French national system of health insurance [21, 22].

These recommendations include an example of 11-item numeric pain scale (0 – no pain, 10 – worst imaginable pain) divided into three levels—light to moderate (0 to 4, light orange code), moderate to intense (4 to 7, orange code), and intense to very intense (7 to 10, dark orange code).

The following narration is used:Your pain treatment has to be taken starting your return home. To evaluate your pain, use the digital scale from 0 to 10. In a case of light to moderate pain (0-4), you should take paracetamol. For moderate to intense pain (4-7), you should take anti-inflammatory or opioid-containing drugs.The treatment is systematic during first 3 days. Prescribed dosage should be respected.

All patients were free to ask any additional questions about pain management at home.

At the end of visit, a diary for data collection is given to a patient, containing the comparator standard pain scale on the first page, and the narration on the second page.

All parents (both from the control and intervention arms) receive a standardized analgesics prescription for at-home pain management, including acetaminophen, ketoprophen (non-steroid anti-inflammatory drug), weak opioid formulation (based on opium), and proton pump inhibitors (gastric protector).

### Intervention description {11a}

The structured education intervention is derived from the well-known and validated 11-items pain intensity scale. The intervention allows the anchoring of each level of pain scale on the individual patient’s experience. In the case of outpatient surgery, patients are empowered to act on medical (post-surgical pain, functional disability) and social constraints (return home, autonomy, home burden, family, no immediate access to a healthcare provider). Patients receive oral, visual (interaction with a clinician), and material support (diary with scale and script), delivered by a clinician, in a standardized manner.

#### Educational intervention development

A cognitive bias where a particular reference point would influence an individual’s decision is known as “anchoring effect” [23]. In patients who need to evaluate their pain intensity regularly, a pain scale anchors modify final judgment and behavior [24–26], especially in chronic pain [27].

Several “comprehensive” patient-developed pain scales are available. Examples include 11-items based Harich’s Comparative Pain Scale [28] and Mankoski Pain Scale [29]. Although not clinically validated, they are used in different pain-related conditions [30–32]. Both scales use anchors for each level of pain from 1 to 10, as examples of common experience (e.g., “average toothache,” ”pinching the fold of skin”) and the ability of daily functions (e.g., “you can still go to work,” “you can no longer think clearly”).

For the purpose of our trial, we used both scales as a prototype for the Comprehensive Acute Pain Anchoring Scale for the Outpatient Orthopaedic Surgery.

We first translated both scales into French, using the process of cross-cultural adaptation of self-reported measures [33]. Two translators (informed – with medical English, and non-informed – no medical English knowledge) were solicited. First, French translation was reviewed conjointly by translators to resolve any discrepancies. Furthermore, another two translators with native English, and naïve to the purpose of the trial, produced a backward translation into English, and discrepancies were resolved. The final version was reviewed by all translators and investigators for the accuracy of used terms and tested for the face validity [34].

Investigators (MD, AB, and RM) used the final translation to create a simplified pain anchor-based scale on the ability to have regular daily activities (home care, meals, sleep). The French version of the produced scale is presented in Additional file 1: Appendix 1.

Based on this scale, an educational intervention was developed conjointly with psychologists (MD, RM). The following psychological concepts were used: a recall of the most intense pain experienced in the past (recall and negativity bias, self-experience anchoring) [35], anchoring or calibration of the individual’s pain experience using a new scale (different pain levels anchoring), and positive suggestions targeting pain management at home [36].

A standard narration was developed containing nine steps (Additional file 1: Appendix 2):Enounce of the purposeRecall of the past pain experienceQuantification of the experience on the scale from 0 (no pain) to 10 (worst imaginable)Qualification of the past pain experience (what was pain felt like)Request to discriminate the weak, moderate, and strong painAnchoring of the recalled pain experience with the experimental scalePrinciples of the transition of mild to moderate and moderate to severe pain explainedPain management principle explained (pain relief, anticipation, medication)Reinsurance

Therefore, the educative intervention consists in standard narration and presentation of the anchoring scale. It is comprehensive in scope, standardized, flexible in content and responsive to an individual’s clinical and psychological needs, and adaptable to the patient’s educational and cultural background [37].

#### Educational intervention delivery

Educational intervention consists of the interaction based on standardized narration and demonstration of the anchoring scale. A standardized narration and sequence is used (Additional file 1: Appendix 2).

Again, all patients were free to ask any additional questions about pain management at home. The average time for this intervention is from 5 to 10 min. At the end of visit, a diary for data collection is given to a patient, containing the experimental scale on the first page, and the narration on the second page.

### Criteria for discontinuing or modifying allocated interventions {11b}

Patients who may wish not to continue the study (consent withdrawal) are free to terminate their participation at any moment. The principal investigator may suspend or withdraw a patient participation for any reason that may conflict with the interest of the patient.

### Strategies to improve adherence to interventions {11c}

Instructions about the purpose of the study and the importance to fill in and to return the diary are thoroughly provided during the inclusion visit. Participating patients will receive a text message via their private e-mail or phone (short message service, SMS) on the day, where their action to fill in the diary is necessary (day 0–day 5, days 10, 20, and 30). The last message on day 30 contains instructions on how to return their diary. Patients are expected to bring the filled diary on day 45 (scheduled surgical visit) or send it by post. Patients are provided with prepaid envelopes in order to send the diary if no postsurgical visit is scheduled on day 45.

### Relevant concomitant care permitted or prohibited during the trial {11d}

Participants are provided with a standard pain treatment order including acetaminophen, ketoprofen, and weak opioids. They are allowed to use any additional medication or non-pharmacological pain relief, in such cases, this should be traced in the diary. In France, the access to non-steroid and opioid analgesics is highly regulated, so the chance that enrolled patients will considerably modify their home treatment is weak. Hypothetically, patients hospitalized during the follow-up period, or deceased, will be considered as lost for follow-up and therefore excluded.

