### Outcomes {12}

The primary outcome is the pain relief measured with a percentage of maximum total pain relief (TOTPAR) over 5 days. TOTPAR is a time-weighted measure of total area under the pain relief curve. This measurement assimilates iterative assessments of a subject’s pain over the duration of the study.

The secondary outcome includes:TOTPAR at day 10, day 20, and day 30 after surgeryThe incidence of severe pain (defined as “severe pain” by the patient)Type, quantity, and doses of taken analgesicsNeuropathic pain prevalence at day 30, detected with DN4 scale [38]The sleep quality measured with Pittsburgh Sleep Quality Index (PSQI) [39] and compared at inclusion day and at the 30th postoperative dayPatients’ perception of postoperative pain management evaluated at with the International Pain Outcome (IPO) questionnaire [40] on day 30 after surgery

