### Participant timeline {13}

Patients are followed for 30 days after the discharge from the hospital (Table 1).

**Table 1 Tab1:** Timeline for patients included in the trial

Actions	Days of study										
	–30 to 0	Surgery	1	2	3	4	5	10	20	30	45
Inclusion/exclusion criteria check	X										
Information and written consent signed	X										
Randomization	X										
Neuropathic pain evaluation	X									X	
Sleep Quality Evaluation	X									X	
International Pain Outcome Questionnaire										X	
At-home diary : - Pain relief, % - Medication taken - Side effects		X	X	X	X	X	X	X	X	X	
Recall SMS/email			X				X	X	X	X	
Diary collection											X

*SMS* short message service

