### Sample size {14}

In the beginning of our study, we were not able to identify any randomized study of educational intervention with TOTPAR as a primary endpoint. It has been reported, that more than 30% of orthopedic patients suffer from “important” pain (e.g., >6/10) during the first 72 h post-discharge [41, 42]. A 2-point change in the 11-item scale or 30% of the difference in pain intensity measurement is defined as clinically significant [43].

We analyzed the literature, reporting the effect of preoperative education on postoperative orthopedic pain in outpatient settings, and available on the year of the study development. Two studies reported the clinically significant effect from the preoperative education, with calculated OR 1.77 [95%CI 1.12–2.79] to 1.97 [95%CI 1.09–3.57] [44, 45]. However, the quality analysis of these studies demonstrated important heterogeneity, the absence of power calculation, small clinical effects, and design flaws.

As we were not able to find any relevant data for the sample size calculation, we have arbitrarily chosen the OR=2 from the effect of preoperative education, which will produce the decrease of proportion of patients with “important” pain from 30 to 17.6%. Giving this assumption, with the risk alpha of 5% and the power at 80%, allocation 1:1, the calculated sample size was 368 patients. We estimate the loss to follow-up at 10%, therefore the 410 patients will be finally enrolled.

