### Statistical methods

#### Statistical methods for primary and secondary outcomes {20a}

Analyses will be performed on an intention-to-treat basis. All data will be checked for normal distribution, and variables will be presented as mean ± standard deviation (SD) or as the median and interquartile range [IQR] accordingly. Categorical variables will be presented as the number and percentage of the total. To compare the two groups, we will use Fisher’s exact test for qualitative data and the non-parametric Mann-Whitney tests for quantitative variables. A comparison of the two groups at randomization will identify potential bias due to unequal allocation. A multivariate logistic regression analysis will be performed to study conditions independently associated with the response to the intervention and to control potential confounding factors. A 0.05 *p* value will indicate statistical significance. Statistical analyses will be performed using R software (R Foundation for Statistical Computing, Vienna, Austria).

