#### Methods in analysis to handle protocol non-adherence and any statistical methods to handle missing data {20c}

No missing data will be accepted for the primary end-point. If there are no measures of pain relief after the postoperative day three registered, but the diary is completed, the TOTPAR will be considered as 100% starting from the next blank page. In a case of missing data for the first three days post-discharge, patients will be replaced by new patients, recruited up to 186-target accrual. Missing data for the secondary endpoints will be examined and the decision guided by a principal investigator and statistician will determine whether these data will be excluded or imputed. In that case, a Multiple Imputation by Chained Equations (MICE) will be performed. A R-software implemented algorithm imputes missing data through an iterative series of predictive models using the other existing variables in the dataset.

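### Excluding every patient hospitalised or deceased within 30 days contradicts intention-to-treat and can discard day 0-5 primary data already recorded

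*Protocol article*

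**What the plan says.** All references are to the protocol article.

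- Section {11d}, on concomitant care: "patients hospitalized during the follow-up period, or deceased, will be considered as lost for follow-up and therefore excluded". The sentence is introduced as hypothetical. It names no cause of admission, no time limit within follow-up, and no outcome to which it is restricted.
- Section {13}: "Patients are followed for 30 days after the discharge from the hospital".
- Section {12}: "The primary outcome is the pain relief measured with a percentage of maximum total pain relief (TOTPAR) over 5 days".
- Section {20a}: "Analyses will be performed on an intention-to-treat basis".
- Abstract, Background, on patients who are poorly informed or cannot follow instructions: "This leads to higher rates of unmet needs in pain treatment, post-discharge emergency calls, and readmissions".
- Section {20c}, on missing primary data: "In a case of missing data for the first three days post-discharge, patients will be replaced by new patients". If nothing is recorded after day three but the diary is otherwise completed, "the TOTPAR will be considered as 100% starting from the next blank page".

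No other section returns hospitalised or deceased patients to the primary analysis.

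**The concern.** Hospitalisation and death occur after randomisation. Removing patients because of them is incompatible with intention-to-treat, and the article states both rules without reconciling them.

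Two consequences follow. First, the exclusion window (30 days) is much longer than the primary window (5 days). Someone admitted on day 12 may have recorded every primary measurement, yet is treated as lost. Second, the exclusion may be informative. The abstract lists readmission among the results of poor pain information, and section {7} hypothesises fewer analgesic side effects with education. On the trial's own reasoning, some admissions could be failures of the kind the education is meant to prevent. If the arms differ in how often this happens, the comparison of those who remain is no longer the randomised comparison. The 10% allowance in section {14} makes up for lost numbers; it does not correct this.

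**Working it through.** **1. The texts side by side.** Exclusion applies from discharge to day 30 ({11d} with {13}). The primary outcome is complete at day 5 ({12}). For an event on days 6 to 30, the primary value does not depend on the event, so exclusion has no justification for that outcome. For an event on days 0 to 5, part of the primary window may be unobserved, and a rule is needed. Exclusion is not one that fits {20a}.

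**2. The plan's own figure.** Section {14} assumes an effect "which will produce the decrease of proportion of patients with “important” pain from 30 to 17.6" per cent, with alpha 5%, power 80% and 1:1 allocation. With the pooled two-sided formula and mean proportion 0.238:

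n per arm = [1.960 × √(2 × 0.238 × 0.762) + 0.842 × √(0.30 × 0.70 + 0.176 × 0.824)]² / 0.124² = 184, or 368 in total, as stated. Then 368 / 0.90 = 409, against 410 stated. The sample size is not in dispute; it only supplies a scale for the next step.

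**3. Illustration on that scale.** The event rates are assumptions. Every excluded patient is taken to be a failure, which is the extreme case. If a proportion h is excluded from an arm with true failure rate p, the rate among those left is (p − h) / (1 − h). For example, (0.30 − 0.05) / 0.95 = 26.3% and (0.176 − 0.02) / 0.98 = 15.9%.

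| Excluded, control / education | Rates after exclusion | Difference (true 12.4) | Power at 184 per arm | Difference when both true rates are 30% |
|---|---|---|---|---|
| 1% / 1% | 29.3% / 16.8% | 12.5 | 82% | 0.0 |
| 2% / 1% | 28.6% / 16.8% | 11.8 | 77% | −0.7 |
| 5% / 2% | 26.3% / 15.9% | 10.4 | 69% | −2.3 |
| 1% / 3% | 29.3% / 15.1% | 14.2 | 91% | +1.5 |

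Differences are control minus education, in percentage points; a negative value in the last column falsely favours control. With 205 per arm (410 / 2), 5% is about 10 patients and 1% about 2.

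**4. Illustration on the TOTPAR scale.** If a proportion h is excluded and those patients have g points less relief than the rest, the arm mean rises by h × g. With an assumed 4% against 1% and an assumed g of 30 to 60 points, the bias is 0.03 × 30 = 0.9 to 0.03 × 60 = 1.8 points. The documents give no standard deviation (SD) for TOTPAR. At 184 per arm the detectable difference in means is (1.960 + 0.842) × √(2 / 184) = 0.29 SD, so any comparison in points needs an assumed SD. With 20 to 25 points it is about 5.8 to 7.3.

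**5. Deleting the rule is not enough.** Take a patient with 60% relief through day 3 who is then admitted and leaves days 4 and 5 blank. Count the window as five equal days for simplicity:

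- 0% relief after the event: 0.6 × 60 + 0.4 × 0 = 36%.
- Section {20c} as written, if the diary counts as completed: 0.6 × 60 + 0.4 × 100 = 76%.
- Worst rank: below every other patient, whatever was recorded.

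These are three different analyses. A patient admitted earlier, with data missing in the first three days, would be replaced under {20c}.

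**The case against.** The strongest reply is that the rule is marked as hypothetical, that the surgery is elective and outpatient, and that equal exclusion creates no difference where none exists (first row of the table). All of that stands, and it means the documents do not show a material effect on the result. It does not make the rule consistent with {20a}. If events are rare, keeping the patients costs almost nothing.

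A reader might infer more than the text supports:

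- *That the rule removes the treatment failures the trial targets.* Admission is for any cause, and readmission is neither an objective nor an outcome of the trial. At most, some failures are removed.
- *That every admission after day 5 loses a complete primary value.* Diaries come back only after day 30, by post or at the day-45 visit ({22} is not needed for this; see {11c} and {18b}). Some hospitalised or deceased patients may never return one.
- *That serious harms leave the dataset.* Section {22} has the surgeon collect adverse effects at the last visit. How this fits with {11d} is unclear, but loss of safety data is not stated.
- *That the bias is a known share of the detectable difference.* That needs assumed event rates, an assumed deficit in relief and an assumed SD. A day-12 admission may have had ordinary relief on days 0-5, in which case data are lost but little bias is added.

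**Conclusion.** The exclusion in {11d} is wrong as written. That rests on the text alone: it conflicts with intention-to-treat, and for events after day 5 it can remove primary data that the event could not have affected. It may also remove some patients whose admission reflects failed pain management or analgesic side effects.

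The size and direction of any bias are unknown, because no event rate is given. Under assumed exclusion of 1% to 5% per arm, with every excluded patient a failure, the planned 12.4-point difference becomes anything from 10.4 to 14.2 points, and a null difference moves by up to 2.3 points. These figures show that the bias can run either way; they are not a forecast.

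**What to change.** 1. Delete the exclusion and state that all randomised patients stay in the primary analysis.
2. Use the day 0-5 diary data whatever happens after day 5. Request the diary from hospitalised patients through the non-return contact already described in {18b}.
3. For admission or death within days 0-5, use diary data up to the event and pre-specify one unfavourable handling: either the worst rank for the whole TOTPAR, or 0% relief for the remaining time. These are different methods, so name one. Add a sensitivity analysis under an alternative handling.
4. State that this overrides {20c} for these patients, so that they are neither replaced nor scored 100% for blank pages.
5. Report known hospitalisations and deaths by arm.

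The cost is protocol and analysis-plan wording, made as a formal amendment under {25} before the final analysis; the article reports 256 patients recruited when it was revised. The downside is a composite reading of the primary endpoint for a few patients: someone admitted for an unrelated reason with good pain relief would be scored unfavourably. The sensitivity analysis shows how much that matters.
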